Screenings visits will take place at the CPMC Addiction Pharmacology Research Laboratory at St. Luke's Hospital (APRL) and will be 1 - 5 hours duration each (approximately 6 hours in total).  Subjects will be inpatient for approximately 70 consecutive hours and the final End-of-Study follow up visit at APRL will take approximately 1 hour.  In total, subject participation will last about 77 hours.  

Subjects will not be paid for any of the screening visits.  For each day or part of a day spent at the CCRC subjects are reimbursed $100.  Subjects will be paid $25 for the follow up visit and will also receive a 20% bonus if they have completed the entire study, making total reimbursement $510.

Purpose:	 	Screening

	Approx. 5 days until CCRC admission	DAY 1
Drug or Placebo Session 1

INPATIENT	DAY 2
Drug or Placebo Session 2

INPATIENT	
DAY 3
Post-dose measures/data collection & Discharge

	                    Approx. 2 weeks	
End-of-Study

Follow-up	
Time:	 	6 hrs over 2-4 visits		10 hrs active
Measures collected 10am-8pm 
	10 hrs active
Measures collected 10am-8pm 
	7 hrs active
Measures collected 9am-4pm
		
1 hr.	
		

	(4b) Procedures: 

Screening Visits: 

Subjects will initially contact the laboratory by telephone.  Following successful initial phone contact, potentially eligible subjects will visit the laboratory.

Depending on the scheduling requirements of the individual, the following 6-hr screening process will take place over 2 to 4 visits:
 
First, the consent is given to the subject to read, reviewed with the subject. Following this subjects will answer the consent questionnaire and will then sign the informed consent. Demographic and screening information will then be obtained. Subjects will then give a sample for urine analysis and females will provide urine for a pregnancy test. The pregnancy test has to be negative for females to participate in the study.   Presence or absence of dependence will be initially determined during the phone screen and confirmed during the on site screening process and physical. 

Questionnaires for estimating use patterns of MDMA, MDA, and other drugs will be administered (i.e., MDMA route of administration and lifetime use questionnaires).  The NEO-FFI is administered to record personality.  A 12-lead EKG, blood and urine samples will be taken.  A brief neurocognitive testing battery is performed. 

Blood testing will include: 
·	Complete blood count
·	Comprehensive blood chemistry panel 

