·	Genotyping for COMT, HTTPLR, 5HT2A, and CYP2D6 

Urine testing will include:
·	Urine toxicology screen (opiates, amphetamine, cocaine, benzodiazepines, MDMA) 
·	Urine pregnancy test for female subjects

Determining CYP2D6 status:  CYP2D6 activity is genetically determined and up to 10% of the Caucasian population has deficient CYP2D6 activity [51].  Either genotyping or phenotyping participants can assess CYP2D6 activity.  Biological samples from subjects will be collected once they are admitted to the GCRC and will be tested for CYP2D6.  
A physician, nurse, or nurse practitioner will conduct a physical examination. 
If necessary, such as in cases where screening results are inconclusive and further tests are needed, additional screening visit(s) may be added.
Experimental sessions:
Experimental sessions at the CCRC at San Francisco General Hospital (SFGH).  Two experimental sessions occur over 2 consecutive days.  Prior to admission and immediately preceding experimental sessions 1 and 2, subjects will be administered a urine toxicology screen and—if female—a pregnancy test.  Timed measurements are made before and after drug administration as described below.  Subjects receive one of two dosing conditions (listed below) per session.  
Subjects are monitored closely before and after, until drug effects resolve or post 8 hours (whichever is later).  
Experimental Drug Doses and Conditions: 
Experimental Dosing Conditions are:
1.	MDA placebo
2.	MDA 98 mg/70 kg body weight
      
Dosing Description and Procedures: In accordance with hospital and other regulations, appropriately licensed personnel will be responsible for administering the study drug.  
Experimental dosing occurs with a 2-hour fast before and a 1.5-hour fast after.  Lactose in a gelatin capsule is used for the MDA placebo.  Placebos are identical in appearance to active drugs.  

Rationale for Experimental Dosing Conditions:  Based on clinical studies, the single MDA dose being given in the present study should produce at most moderate intoxication and stimulant effects that should resolve within 8 hours.  Similar MDA doses have been used in other studies.  The dose is slightly lower than used in our MDMA studies to account for the lower molecular weight of MDA vs. MDMA and facilitate comparisons.

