Source and Storage of study drugs:  Under supervision of the Food and Drug Administration, we will synthesize MDA in our laboratory.  We will assess identity, stability, and purity to their satisfaction.  MDA will be stored and handled according to federal, state, and local regulations. MDA will be stored in our safe using procedures approved by the DEA.

Study Measures are similar or identical to those used in our past and ongoing studies to facilitate comparisons between MDA and related compounds.  Below we list timing of measures followed by measure descriptions.
Timing of Measures:
Plasma for MDA & Metabolites: Pre and 1, 2, 4, 6, 8, 12, 26, and 30 hrs after MDA or Placebo.
Urine for MDA & Metabolites: Urine samples at 0-8 and 24-48 hrs after MDA or Placebo dosing..
Plasma or serum (as appropriate) for oxytocin (which will be frozen and sent to [name]): Predose and 1, 2, 3, and 4 hours after dosing.  
Plasma or serum (as appropriate) for cortisol and prolactin: Predose, 2, and 3 hours after dosing.  

Heart rate, blood pressure, impedance cardiography, skin and core temperatures, visual analogue scales: Predose and 0.5, 1, 1.5, 2, 2.5, 3, 4, 6, 8, 24, and 30 hours after dosing 
BSI: Predose and 24 hours after MDA or Placebo (to measure possible residual drug effects).
Subjective drug effects questionnaire (SDEQ): At 7 hours after dosing and before discharge on Day 3. 
APZ-OAV and Hood M-Scale:  At 7.5 hours after dosing and before discharge on Day 3.
AVI and IAS-R: Predose, 2.5, 7.5 and 29 hrs after dosing and before discharge on Day 3.
Brief Fear of Negative Evaluation (BFNE) and State-Trait Anxiety Instrument – State (STAI):  Predose and once during peak drug effects (1 – 2.5 hours postdose).
Emotional Face Task and Famous Face task: During peak drug effects (1 – 2.5 hours postdose).
Dot Probe Task:  at 2hr. post dose.
Neurocognitive battery (Visual Functioning Battery):  3 hours after MDA or Placebo (to measure possible residual drug effects).
EEG:  3 hrs after MDA.
Written description of drug effects:  10 hours after dosing.

Descriptions of Measures
Pharmacokinetic and Hormonal Measures
Blood is sampled through an indwelling intravenous catheter placed by licensed medical personnel.  Each sample requires 7 ml or less, making the total required in each of the two experimental sessions 146 ml.
All urine is collected, with the pH determined before acidification and storage with timed samples reflecting predose and the 0-8 and 8-30 hrs after MDA.

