Nonetheless, it will be common knowledge that participants in this experiment are required to have past use of MDA or MDMA.  Therefore, in the consent form and in discussions, we caution potential participants that anyone having strong concerns about their past use of drug use being revealed should not participate in this research.  To minimize these risks, we are applying for a Certificate of Confidentiality.  

PROTECTION AGAINST RISK

Volunteer Discontinuation, Dropout or Dismissal.  A volunteer may drop out of the study at any time if he/she so chooses or if the investigator feels it is clinically appropriate.  A volunteer will be dismissed from the study due to a serious or unexpected adverse experience or a serious concurrent illness that warrants withdrawal of the subject from the study.  Subjects who use illicit drugs that could interact with study drugs or who otherwise fail to follow study procedures can be dismissed.  

Subject Safety Monitoring and Test Termination.  Using self-report questionnaires and a general medical exam with a physician, nurse, or nurse practitioner, subjects will be screened to eliminate those with significant medical or psychiatric problems.  Special attention is given to allergies and past adverse reactions to MDA, MDMA, and any other stimulants or hallucinogens. If adverse effects should occur, medical treatment will be immediately available. We have extensive experience in measurements in pharmacology/pharmacodynamic studies. A hospital maintained crash cart, oxygen and emergency ventilation equipment (Ambubags) are immediately available. Physiological monitoring of blood pressure, heart rate, body temperature, and subjective ratings will be carried out before dosing and until acute effects resolve (typically around 6 hrs) to ensure that there are no serious adverse physical or psychological effects of MDA.  Throughout the study, particular attention is paid to the rare MDMA-related acute hyperthermia that might also occur with MDA.  Methods of protecting against this risk are described below. 

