Hyperthermia:  We monitor core and skin temperature.  Core temperature is measured with a swallowed disposable transmitter (mini-Mitter or similar).  If the disposable transmitter is not functioning properly, tympanic temperature will be recorded using infrared tympanic device.  The two temperatures (and ambient temperature) are displayed continuously during the session for safety monitoring.  Skin temperature is monitored with a thermocouple touching an appropriate surface.  For scientific purposes, temperature is recorded at scheduled intervals after MDA, as described above.
Risk factors for hyperthermia are believed to include high drug dose, dehydration, exercise, and high ambient temperature.  For example, Henry and Rella (2001) write that “it seems apparent that cases of severe hyperthermia and deaths from heatstroke [after MDMA use] were due mainly to prolonged dancing without rest and without drinking enough liquid to allow for normal temperature control through sweating.”  All these risk factors will be absent in our clinical setting.

Definition of dose-limiting toxicity:  Vital signs will be frequently monitored with blood pressure and temperature.  If we exceed stopping criteria in more than one subject we will stop all dosing pending review by all regulatory parties.  The stopping criteria are:
1.	HR > 160, or < 40 or the degree of change is more than 40% from baseline.
2.	SBP > 180, or < 80 or the degree of change is more than 40% from baseline.
3.	DBP > 105, or < 50 or the degree of change is more than 40% from baseline.
4.	Respiratory rate > 28 or < 8, core temperature change > 1 degree C.

In addition, the study will be stopped if any of these serious adverse events occur:
1.	[Na+] ± 6 mEq/L in 12 h
2.	[Na+] ± 6 mEq/L between sessions
3.	Confusion, agitation, delirium, uncontrolled anxiety or aggression.
4.	Muscle weakness, convulsion, or any type of involuntary motor dysfunction.
5.	Reported palpitations, chest pain or chest oppression, flushing, or fainting.
6.	Uncontrollable headache, discomfort, nausea, or vomiting.
7.	Any other serious adverse effect regarded as being due to MDA.

Safety (Go/No Go) Criteria: We have developed conservative criteria to determine the safety of allowing participation in the study and, once accepted, for administering MDA.  Criteria are assessed on admission and prior to dosing with MDA  

The criteria for administering MDA are:

1.	Satisfy inclusion/exclusion criteria (listed above)

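### Two study-stopping rules depend on a 6 mEq/L change in sodium, but no sodium sample is scheduled in either session and no reference value is stated

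*Protocol*

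**What the plan says.** The serious-event list under Definition of dose-limiting toxicity (protocol section 5b) stops the study if any one item occurs. Its first two items are numeric: "Na+] ± 6 mEq/L in 12 h" and "Na+] ± 6 mEq/L between sessions".

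The places where sodium data could come from are these:

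- **Timing of Measures (4b).** Session blood is listed for three purposes: "Plasma for MDA & Metabolites: Pre and 1, 2, 4, 6, 8, 12, 26, and 30 hrs after MDA or Placebo"; oxytocin at predose and 1, 2, 3 and 4 h; and "Plasma or serum (as appropriate) for cortisol and prolactin: Predose, 2, and 3 hours after dosing". Urine is for MDA and metabolites.
- **Experimental sessions (4b).** The tests before each session are urine toxicology and, for women, pregnancy.
- **Subject Safety Monitoring (5b).** "Physiological monitoring of blood pressure, heart rate, body temperature, and subjective ratings will be carried out before dosing and until acute effects resolve".
- **Go/No Go criteria (5b).** Eligibility, urine toxicology and vital signs, assessed on admission and before MDA dosing.
- **Screening Visits (4b).** The blood tests include a "Comprehensive blood chemistry panel". The study schedule places screening at "Approx. 5 days until CCRC admission".

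Section 5b also describes hyponatremia in illicit MDMA users and calls it unlikely in this controlled setting.

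**The concern.** A stopping rule on a change needs at least two values and a statement of which one is the reference. The 12-hour rule needs two sodium values within 12 hours. The between-session rule needs at least one value in each session. The protocol schedules none of these and does not say what the change is measured from.

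These two items stand apart from the symptom items in the same list and are not worded as symptom-triggered. Anyone relying on the list would believe that a silent fall or rise in sodium stops dosing of later subjects. Following the plan as written, nobody would see the change. A sample drawn because of symptoms would have no in-session baseline to compare with.

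This is not a detail that a statistical analysis plan would normally supply. Safety sampling times belong in the protocol.

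**Working it through.** **1. Data needed against data scheduled**

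| Rule | Minimum data needed | Scheduled in the sessions |
|---|---|---|
| Change within 12 h | two values within 12 h | none |
| Change between sessions | one value per session | none |

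With 12 subjects and two sessions each, 12 × 2 = 24 sessions contain 0 scheduled sodium values. The screening panel precedes admission by about 5 days, so it falls in neither comparison window.

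**2. Is there room in the blood budget?**

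The protocol's own total reproduces: 51 + 2 × 146 = 343 ml.

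- Listed samples per session: 9 (MDA) + 5 (oxytocin) + 3 (cortisol and prolactin) = 17. At 7 ml or less each, that is at most 17 × 7 = 119 ml.
- Counted session by session, at least 146 − 119 = 27 ml is assigned to no listed assay, or 54 ml over two sessions.
- Sessions start 24 h apart, so the 26 h and 30 h draws of session 1 fall at the 2 h and 6 h draws of session 2. If each pair is drawn once, there are 34 − 2 = 32 samples, at most 32 × 7 = 224 ml of 2 × 146 = 292 ml. That leaves at least 68 ml.
- Sodium at predose, 4 h and 8 h: 2 × 3 × 7 = 42 ml at most. With the 12 h draw: 2 × 4 × 7 = 56 ml at most.

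So 42 ml fits under either count, and 56 ml fits if the coinciding draws are shared. If none of the unassigned blood is free, the study total rises from 343 ml to at most 385 or 399 ml.

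**3. What would monitoring do by chance alone?**

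The protocol gives no within-person SD for sodium, so 1.0, 1.5 and 2.0 mEq/L are assumptions. Assume no true change, independent normal errors, samples at predose, 4, 8 and 12 h in both sessions, and a stop at a change of 6 or more.

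There are 7 comparisons per subject: 3 changes from predose in each session, plus predose to predose. The difference between two values has SD √2 × SD. For SD 1.5 that is 2.12, so 6/2.12 = 2.83 and one comparison trips with probability 0.0047. Seven of them give an upper bound of 0.033. Simulation, which allows for the shared predose value, gives p = 0.0290 per subject. Over 12 subjects, 1 − (1 − 0.0290)^12 = 30%.

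| Assumed SD (mEq/L) | p per subject, no repeat | 12 subjects, no repeat | p per subject, confirmed by repeat | 12 subjects, confirmed |
|---|---|---|---|---|
| 1.0 | 0.00015 | 0.2% | 0.000002 | below 0.1% |
| 1.5 | 0.0290 | 30% | 0.0023 | 3% |
| 2.0 | 0.1795 | 91% | 0.0316 | 32% |

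Confirmed means that one repeat of the later sample also shows a change of at least 6 from predose in the same direction.

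Two variations without a repeat:

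- With predose, 4 h and 8 h only, the 12-subject figures are 0.1%, 23% and 83%.
- If the laboratory reports whole mEq/L (also an assumption), the four-sample figures become about 1%, 52% and 97%.

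The choice of reference matters too. If any pair of values within a session counts, the four-sample figures are 0.3%, 46% and 98%.

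**The case against.** The strongest reply is that Timing of Measures is a list of research measures, not a full safety schedule. It omits urine toxicology, pregnancy tests, the inpatient CYP2D6 samples, continuous ECG and respiratory rate, all of which appear elsewhere. The session blood volume exceeds the listed draws, and section 5b counts blood at follow-up for which no assay is named. Sodium samples could therefore be intended but not itemized. This stands as a caution about reading intent. It supplies no sampling time, because the protocol assigns the spare blood to nothing. The comparison with respiratory rate is also weak: that can be read at the bedside at any moment, whereas sodium needs a drawn sample and a laboratory result.

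A second reply is that Go/No Go item 1 requires the eligibility criteria to be met before dosing, and inclusion criterion 5 cites blood chemistry. On the most generous reading this gives a predose value. No repeat panel is listed, however, and no change within 12 hours of a dose can follow from it.

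A reader might infer that sodium can never be assessed in this trial, or that subjects are unprotected against hyponatremia. The documents support neither. A for-cause sample is not excluded. Confusion, delirium and convulsion are stopping events that need no laboratory value, and subjects are inpatients. On dosing, "Subjects receive one of two dosing conditions (listed below) per session", so each subject has one MDA exposure. A reader might also infer that added sodium tubes must break the blood allowance. The arithmetic does not show that, since coinciding draws may be shared and samples are 7 ml or less.

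The false-stop risk is a fair objection to adding samples without safeguards, and the fix has to meet it.

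**Conclusion.** The point holds, and the protocol should be amended. Two mandatory stopping rules, each triggered by one occurrence, have no scheduled post-dose sodium data and no stated reference value. Zero sodium samples are scheduled in 24 sessions, and the most generous reading of the eligibility re-check adds only a predose value. The consequence is confined to a symptomless change going unseen and so not stopping later dosing. No efficacy, pharmacokinetic or pharmacodynamic conclusion depends on it, and the protocol itself regards the event as unlikely.

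This conclusion rests on the text alone and on none of the assumed SDs. Those figures bear only on how the remedy should be built: from 0.2% to 91% for a false stop without confirmation, and from below 0.1% to 32% with it, under the four-sample schedule.

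**What to change.** 1. Add serum sodium to Timing of Measures at predose, 4 h and 8 h in both sessions, all at existing draw times, with results returned promptly. Add the listed 12 h draw if it is taken. With dosing at about 10 am it falls near 10 pm, beyond the stated 10-hour limit on the catheter, so it would need a separate puncture.
2. Define the within-session change as relative to that session's predose value.
3. Before dosing in session 2, compare its predose sodium with the session 1 predose value.
4. Require a prompt repeat sample for any change of 6 mEq/L, hold further dosing until it is read, and stop the study only if the repeat confirms the change. This should be mandatory, because one unconfirmed value could otherwise end a 12-subject study.

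Cost: a short amendment; 24 × 3 = 72 or 24 × 4 = 96 routine assays, plus any repeats; and at most 7 ml per sample (42 or 56 ml per subject before repeats), possibly within the volume already stated. Some chance of a false stop remains even with confirmation. The sponsor should judge it against the within-person SD of its own laboratory's sodium results.

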Who and Why:  Subjects will be healthy, males or females between the ages of 18 and 50. Subjects will be experienced with either MDA alone or both MDMA and a hallucinogen.  Experience is defined as use on at least 3 occasions.  In recruiting and selecting, we will not discriminate based on sex, race, or ethnic background.  Subjects will be excluded if any significant abnormalities are uncovered in medical or psychiatric examination or in the laboratory screening profiles. No volunteer will be accepted into the study if they are currently trying to stop their use of amphetamines, hallucinogens, or MDMA-like drugs.    

Inclusion Criteria
1.	Healthy males or females aged 18 to 50 years. Females should be either non-childbearing (tubal ligation or total hysterectomy) or of childbearing potential using one or more of the following methods of contraception: abstinence, male or female condoms (with/without spermicide), hormonal contraceptives, cervical cap, diaphragm (with spermicide) and/or copper containing intrauterine device (with/without spermicide). No other contraceptives are acceptable.
2.	Experienced with either MDA or both MDMA and a hallucinogen, defined as a minimum of 3 episodes of use with no more than four tablets per occasion of use. 
3.	Must be a fluent English speaker.  The tests in our neurocognitive battery have only been validated in English speakers therefore we will include only fluent speakers.
4.	Willing and able to give written consent
5.	Healthy without medical contraindications to MDA determined by the following: medical history, physical examination, 12-lead ECG, hematology, blood chemistry, and urinalysis
6.	Blood liver transaminase elevations up to 3 times the upper limit of normal will be acceptable.
7.	For females, a negative pregnancy test at screening and prior to each experimental session.

Exclusion Criteria
1.	Current enrollment in a MDA, alcohol, or other drug treatment program or current legal problems relating to MDA, alcohol, or other drug use, including awaiting trial or supervision by a parole or probation officer.
2.	Subjects with a past-history of using only low doses of MDMA or MDA (i.e. have only used less than 1 tablet).
3.	Current dependence on any other psychoactive drug (except nicotine and caffeine)

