4.	Significant physical or psychiatric illness which might impair the ability to safely complete the study or that might be complicated by the study drugs, including prior seizures (after age 8) or other active neurological disease or clinically significant abnormalities on physical examination or screening laboratory values
5.	Likelihood of needing medications to treat an illness during the study period
6.	Body Mass Index > 30 or < 18
7.	HIV seropositive by self-report
8.	Pregnancy or lactation
9.	History of serious adverse event or hypersensitivity to MDMA or MDA. 
10.	Currently taking any medication other than over-the-counter nonsteroidal antiinflammatories, topical medications, inhaled asthma therapy, and over-the-counter nonsedating antihistamines, or hormonal contraceptives.
11.	Any other medical or psychosocial condition that would preclude useful, safe, or consistent participation.

Initial eligibility is determined over the course of several screening visits.  After informed consent is obtained, potential volunteers are conservatively screened by the researchers using health history and psychological questionnaires, urine and blood assays, and interview with a physician, nurse practitioner, or nurse.  Medical screening includes history and physical, blood cell count, Chemistry panel, and 12-lead EKG.  

Subjects are not eligible for concurrent drug administration research studies.

	(4e) Subject Recruitment and Initial Contact Method: 

Prospective subjects will contact the researchers.  Subjects will be recruited from advertisements placed in Bay Area newspapers, fliers, radio, and community Internet sites (such as Craigslist.org), asking for volunteers to participate in studies of MDA effects.  Copies of proposed advertisements are attached.

5.	HUMAN SUBJECTS: 

(5a) Consent Process and Documentation:  

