2.	Urine toxicology reveals no recent use of MDA or other related drugs 
3.	Have vital signs with heart rates <100 and >50 and systolic blood pressure <135 and >95 and diastolic blood pressure <85 and >50 and respiratory rate <20 and >10; tympanic temperature of 37±0.5˚C and arterial O2 saturation <92%. 

Any severe adverse events will be promptly reported to all relevant regulatory (IRB, FDA, CRAP, CHR) and funding (NIDA) agencies.

Treatment and Compensation for Injury. This will be according to standard CPMC policy.  

(5c) Alternatives: 

This is research, not treatment.  The alternative is to not participate.

6.	QUALIFICATIONS OF INVESTIGATORS: 

[name] has experience administering closely related drugs (MDMA and methamphetamine) to human subjects in protocols similar to the one presented here.  [name] has expertise in pharmacology and has conducted research with MDMA users that did not involve drug administration.  [name] has conducted research similar to this one with [name] for many years.  

7.	BIBLIOGRAPHY: 

1.	de la Torre, R., et al., Pharmacology of MDMA in humans. Ann N Y Acad Sci, 2000. 914: p. 225-37.
2.	Camilleri, A.M. and D. Caldicott, Underground pill testing, down under. Forensic Sci Int, 2005. 151(1): p. 53-8.
3.	Roberts, A.F. and F. Alexander, Report on Clinical Evaluation of SKF#5 (Amphidoxamine). 1957, maps.org online bibliography.
4.	Naranjo, C., A.T. Shulgin, and T. Sargent, Evaluation of 3,4-methylenedioxyamphetamine (MDA) as an adjunct to psychotherapy. Med Pharmacol Exp Int J Exp Med, 1967. 17(4): p. 359-64.
5.	Turek, I., R. Soskin, and A.A. Kurland, Methylendedioxyamphetamine (MDA) subjective effects. J Psychedelic Drugs, 1974. 6(1): p. 7-13.
6.	Yensen, R., et al., MDA-assisted psychotherapy with neurotic outpatients: a pilot study. J Nerv Ment Dis, 1976. 163(4): p. 233-45.
7.	Zinberg, N., Observations on the phenomenology of conscious change. Journal of Psychoactive Drugs, 1976. 8(1): p. 59-76.
8.	Naranjo, C., The healing journey: new approaches to consciousness. 1973, New York: Pantheon Books.
9.	Jackson, B. and A. Reed, Jr., Another abusable amphetamine. Jama, 1970. 211(5): p. 830.
10.	Shulgin, A.T., Psychotomimetic drugs: Structure–activity relationships, in Handbook of Psychopharmacology, Vol. 11, L.L. Iversen, S.D. Iversen, and S. Snyder, Editors. 1978, Plenum Press: New York. p. 243-333.

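### The pre-dose safety gate requires oxygen saturation below 92%: the inequality is reversed, so normally saturated subjects fail the clause

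*Protocol*

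**What the plan says.** In Protocol section 5b, the paragraph on Safety (Go/No Go) Criteria states its purpose: "We have developed conservative criteria to determine the safety of allowing participation in the study and, once accepted, for administering MDA". It gives the timing as well: "Criteria are assessed on admission and prior to dosing with MDA". The list then opens with "The criteria for administering MDA are", followed by three items.

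- Item 1 requires that the inclusion and exclusion criteria are satisfied.
- Item 2 requires a urine toxicology result free of recent use of MDA or related drugs.
- Item 3 gives the vital signs the subject must have. It begins "Have vital signs with heart rates <100 and >50 and systolic blood pressure <135 and >95 and diastolic blood pressure <85 and >50", continues with a respiratory rate between 10 and 20 and a tympanic temperature of 37±0.5 °C, and ends with "arterial O2 saturation <92" per cent.

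**The concern.** Each item on the list is a condition to be met before MDA is given. Read in the same way as the terms beside it, the saturation term requires a value below 92%. That is the opposite of what a safety gate for healthy volunteers should require.

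This is an operative threshold for giving a drug whose cardiovascular and hyperthermia risks the protocol itself discusses. If staff follow the text, a normally saturated volunteer cannot be dosed. If they do not, either each dose departs from a written safety criterion, or each member of staff substitutes a personal reading of it. In the second case nothing in the document fixes the limit that was actually applied.

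**Working it through.** The protocol gives no derived figure to reproduce here. The check is a reading of the clause against its neighbours, its stated purpose and the rest of the document.

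**1. Is the list permissive?** Yes. The lead-in names criteria for giving the drug, items 1 and 2 are conditions to be satisfied, and item 3 states what the subject's vital signs must be.

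**2. How do the six terms of item 3 compare?**

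| Sign | Lower limit | Upper limit |
|---|---|---|
| Heart rate | 50 | 100 |
| Systolic pressure | 95 | 135 |
| Diastolic pressure | 50 | 85 |
| Respiratory rate | 10 | 20 |
| Tympanic temperature (37 ± 0.5 °C) | 36.5 | 37.5 |
| Arterial O2 saturation | none | 92% |

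Five signs have two limits each (5 × 2 = 10 bounds) that enclose an acceptable range. Saturation alone has one bound, and that bound is an upper one. No single reading makes all six terms sensible. As conditions for dosing, the saturation term is wrong. As reasons to withhold the drug, the other five are wrong.

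**3. What does the clause do to given values?**

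| Saturation | As printed (<92%) | With the sign turned (>92%) |
|---|---|---|
| 88% | passes | fails |
| 91% | passes | fails |
| 92% | fails | fails (passes under ≥92%) |
| 95% | fails | passes |
| 98% | fails | passes |
| 100% | fails | passes |

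The documents give no normal range for saturation. I assume about 95–100% for a healthy adult at rest. The conclusion does not depend on that choice: as printed, every value at or above 92% fails.

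**4. Does anything else in the protocol correct it?** No. Saturation is mentioned only here. The stopping criteria in section 5b cover heart rate, systolic and diastolic pressure, respiratory rate and core temperature. The physiological monitoring described under Protection Against Risk covers blood pressure, heart rate and body temperature. Neither includes saturation.

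**5. Could it be an error in reading the PDF?** Unlikely. Both inequality signs appear correctly several times in the same sentence.

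**6. How many decisions does it govern?** Section 4a plans 12 subjects, and section 4b gives each of them placebo in one session and MDA in the other.

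- MDA doses: 12 × 1 = 12.
- Pre-dose checks, if the list is applied before both sessions because the study is blinded (assumption): 12 × 2 = 24.
- The text also calls for assessment on admission. One admission per subject would add 12, giving 24 + 12 = 36.

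**The case against.** The best case on the other side concerns weight. This is very probably a typing error that any clinician would notice. It does not fail dangerously: the conditions are cumulative, so a desaturated subject would still have to satisfy the eligibility criteria and the other vital-sign limits. Section 5b also provides for medical screening and for oxygen and ventilation equipment at hand. Read literally, the clause withholds drug from healthy people; read as evidently meant, it works as an ordinary gate. Neither reading biases the data.

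All of that stands, and it limits the likely harm. It does not make the text right. Compliance is judged against the written criterion, and this is the protocol's only saturation limit.

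Two narrower points also stand.

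- The conflict with the eligibility criteria in section 4d is one of inference. Inclusion criterion 5 ("Healthy without medical contraindications to MDA determined by the following: medical history, physical examination, 12-lead ECG, hematology, blood chemistry, and urinalysis") and exclusion criterion 4 ("clinically significant abnormalities on physical examination or screening laboratory values") do not mention saturation. They show only that the trial intends to enrol healthy people. The finding therefore rests mainly on the list's stated conservative purpose and on the five parallel terms in item 3.
- The context makes the intended direction clear, although no other section states a saturation limit. That makes the correction safe to specify.

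**Conclusion.** The concern holds. One of the six vital-sign terms in item 3 is printed with its inequality reversed. The clause is met only by saturations below 92% and failed by every value from 92% upward, against the stated purpose of the list.

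It bears on the MDA dose of all 12 subjects. The larger counts depend on how the list is applied under blinding and at admission. The conclusion needs only the assumption that normal saturation lies at or above 92%.

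The practical consequence is a gate that almost no eligible subject could pass as written, and hence protocol deviations or undocumented reinterpretation. The statistical design is untouched. It must be corrected because it is an operative safety threshold and the correction is unambiguous.

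**What to change.** In Protocol section 5b, Safety (Go/No Go) Criteria, item 3, turn the sign so that the term requires arterial O2 saturation >92%. If a reading of exactly 92% is meant to be acceptable, use ≥92%. Make the change before the first dose, and carry it into any dosing checklist or case report form that copies the list.

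The cost is a one-character protocol amendment, with no change to design, sample size or analysis.
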